**Methods/design:**

This double-blind, randomized controlled clinical trial aims to recruit patients who have undergone abdominal surgery and experienced postoperative dysmotility to evaluate the efficacy and safety of XBP for preventing POI and accelerating recovery. The research will tackle the common problem of slow recovery of gastrointestinal function after surgery. The participants will be patients who undergo laparoscopic radical resection of rectal carcinoma or laparoscopic panhysterectomy of a benign lesion. Primary outcome measures will be time to first flatus, defecation, normal bowel sounds, and liquid/semi-liquid/general diet. Good Clinical Practice (GCP) standards of efficacy and safety will also be evaluated, along with objective investigation of the mechanism of action of ghrelin.

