### Trial procedure

The entire trial will include a preoperative assessment, an intervention phase (generally 1–7 days), and a 2-month follow-up phase. Included subjects will be randomized to groups receiving XBP or a placebo, using a stratified random system, and acquire a random number (corresponding to numbered drugs) in this phase. Participants will be instructed to take the medicine twice every day after surgery (excluding the surgery day) at 09:00 and 16:00 until defecation occurs. Any remaining medicine will be recovered and recorded. Subjects will be evaluated at least three times per day (between 01:00 and 09:00, 09:00 and 17:00, and 17:00 and 01:00) and the results recorded in a Case Report Form (CRF) until they leave the hospital. The participant flowchart is shown in Fig. 1 and the Standard Protocol Items: Recommendations for Interventional Trials (SPIRIT) Figure for the trial is shown in Fig. 2. Adverse events will be monitored by telephone calls to subjects on the 14th and 60th days after surgery.

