### Outcome measures

1. Primary outcome measures: time to first flatus, time to first defecation, time to first bowel sounds, time to consuming liquid/semi-liquid/general diet

2. Secondary outcome measures: gastrointestinal symptoms, such as abdominal distention and pain, nausea, vomiting; serum hormone levels, including ghrelin, motilin, corticotropin-releasing hormone, and bradykinin; electrogastrogram

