### Data collection and statistical analysis

Data will be collected from participants via daily face-to-face and telephone interviews and recorded in the CRFThe statistical package, Epidata 3.1, will be used for data entry. Two people will perform data entry independently, and they will be trained in advance and pass a test before they begin the work. The data will then be transferred to Statistical Package for the Social Sciences (SPSS) software for data analysisThe statistical analyses were pre-specified and performed on an intention-to-treat (ITT) basis. The ITT analysis will include all patients who were randomly recruited, and the per-protocol (PP) analysis includes patients who completed the study and did not have major protocol violations. All analyses are based on the ITT population, and the result of the ITT analysis is compared with the PP analysis to assess the sensitivity. All missing data are analyzed using the last observation carried forward (LOCF) imputation method. Changes from baseline in outcome measurement among the two groups are analyzed using analysis of variance (ANOVA) or the Kruskal-Wallis test when appropriate. The Bonferroni methods for multi-comparisons are performed if the tests are statistically significant. Safety analysis is analyzed mainly using descriptive statistics. All statistical tests are in a two-tailed t test at a 5% level of significance (Additional file 1).Data will be analyzed by an independent statistician. Data for continuous variables are reported using mean (standard deviation; SD) for normally distributed data or median (range) for skewed data. Data for categorical variables are expressed as number (percentage). Intergroup differences are assessed for significance using Student’s *t* test for normally distributed continuous variables or the Mann-Whitney U test for skewed continuous variables. Intergroup differences in categorical data are assessed using the *χ*^2^ test or Fisher’s exact tests (two-tailed), as appropriate. Length of hospital stay is calculated using Kaplan-Meier analysis to compare differences between groups. Data are analyzed using SPSS 19.0 (IBM, Armonk, NY, USA), with the threshold of significance defined as a two-tailed *p* < 0.05.

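### Where the plan analyses change from baseline, it compares the raw change between arms without adjusting for baseline; a baseline-adjusted model would be at least as precise for the secondary outcomes, at almost no cost

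*Protocol article*

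**What the plan says.** All of this is in the protocol article.

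- **Rule for change.** Data collection and statistical analysis: "Changes from baseline in outcome measurement among the two groups are analyzed using analysis of variance (ANOVA) or the Kruskal-Wallis test when appropriate".
- **Rule for continuous variables in general.** The same section says "Intergroup differences are assessed for significance using Student’s" t test if the data are normally distributed, "or the Mann-Whitney U test for skewed continuous variables".
- **Level.** "All statistical tests are in a two-tailed t test at a 5% level of significance".
- **Outcomes.** Under Outcome measures, the primary list begins "Primary outcome measures: time to first flatus, time to first defecation, time to first bowel sounds" and continues with times to diet stages. The secondary list has gastrointestinal symptoms, then "serum hormone levels, including ghrelin, motilin, corticotropin-releasing hormone, and bradykinin; electrogastrogram".
- **Aim.** The abstract's Methods/design paragraph says efficacy and safety will be evaluated "along with objective investigation of the mechanism of action of ghrelin".
- **Baseline visit.** Trial procedure: "The entire trial will include a preoperative assessment". The text does not list what that assessment contains.

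The article names no analysis of covariance, baseline covariate or other adjusted model.

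**The concern.** A raw change score subtracts the whole baseline value, which amounts to fixing the regression slope on baseline at 1. If the true slope is lower, as it is when baseline and follow-up are only moderately correlated and equally variable, the subtraction adds baseline noise to the comparison. A chance difference between arms at baseline is then over-corrected through regression to the mean. A model that estimates the slope from the data avoids both problems.

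What is at stake is the width of the confidence intervals, and the power, for the secondary measures. Serum ghrelin matters most here, because it is the listed outcome that directly measures the mechanism named in the abstract. The sample size rests on time to first flatus alone and no power is claimed for the hormones, so there is no stated reserve of precision to draw on.

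**Working it through.** **Which outcomes the rule reaches.** A change from baseline needs a baseline value. Times to flatus, defecation, bowel sounds and diet have none. That leaves the hormones, the electrogastrogram and any symptom recorded as a score. Symptoms recorded as present or absent would fall under the plan's chi-square or Fisher rule.

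**The plan's own figures.** None is given for these outcomes. The sample-size section reproduces as far as it can be checked: 89/(1 − 0.15) = 104.7, so 105 per group, and 4 × 105 = 420, or 210 per treatment arm. The 89 cannot be checked because no standard deviation or power is stated. Nothing below depends on it.

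**General result.** Let sX and sY be the within-arm standard deviations at baseline and follow-up, and rho their correlation.

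- Change score: Var = sX² + sY² − 2·rho·sX·sY
- Baseline-adjusted (ANCOVA): Var = sY²(1 − rho²)
- Difference: (sX − rho·sY)², which is never negative and is zero only when the true slope rho·sY/sX equals 1

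So, apart from the one degree of freedom spent on the covariate, adjustment cannot lose precision.

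**Equal standard deviations (assumed).** The ratio is R = (1 − rho²)/[2(1 − rho)] = (1 + rho)/2. If the change-score test has 80% power (assumed) at two-sided 5%, the adjusted power is Φ[(1.960 + 0.842)/√R − 1.960].

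| rho (assumed) | R | Fall in standard error | Adjusted power | Adjusted n per arm matching 210 by change score |
|---|---|---|---|---|
| 0.3 | 0.65 | 19% | 93.5% | 137 |
| 0.5 | 0.75 | 13% | 89.9% | 158 |
| 0.7 | 0.85 | 8% | 86.0% | 179 |
| 0.9 | 0.95 | 2.5% | 82.0% | 200 |

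A simulation with normal data (4000 runs, 178 = 2 × 89 per arm) agrees. Power for ANOVA on change, Kruskal-Wallis on change and ANCOVA was 0.80/0.79/0.93 at rho 0.3, 0.80/0.78/0.90 at 0.5 and 0.81/0.78/0.86 at 0.7.

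**Unequal standard deviations.** With k = sY/sX, R = k²(1 − rho²)/(1 + k² − 2·rho·k).

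- rho 0.5, k 1.5: 2.25 × 0.75/(1 + 2.25 − 1.5) = 1.6875/1.75 = 0.96, a gain of about 4%.
- rho 0.7, k 1.3: 1.69 × 0.51/(1 + 1.69 − 1.82) = 0.8619/0.87 = 0.99, a gain of about 1%.
- rho 0.5, k 0.8: 0.64 × 0.75/(1 + 0.64 − 0.8) = 0.48/0.84 = 0.57, a gain of about 43%.

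**Against follow-up alone.** If a hormone were instead compared by a t test on the post-treatment value, the ratio is 1 − rho², whatever k is: 0.91 at rho 0.3 (80% power becomes about 84%) and 0.75 at rho 0.5 (about 90%). The change score is noisier than the follow-up value alone when rho < 1/(2k), which is rho < 0.5 only if k = 1.

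**The case against.** Several points on the other side stand.

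- **The rule names no outcome.** It does not mention hormones or the electrogastrogram. A reader might infer that the plan expressly assigns them to raw change scores; it does not. The link is by elimination, and the t test or Mann-Whitney rule could be the one meant. That rule is unadjusted too, so the point survives, but the gain is then the 1 − rho² comparison.
- **Baseline sampling is implied, not stated.** The visible text gives before-and-after timing only for the safety tests. The schedule figure is not shown, so the point is conditional on a baseline value existing for each measure.
- **Further detail may exist.** The section cites an additional file that is not shown, and covariates are often left to an analysis plan. This helps only in part, because the article positively fixes a method and calls its analyses pre-specified.
- **Validity is not at issue.** A reader might infer bias or a raised false-positive rate. Under randomization the change-score comparison is unbiased and keeps its type I error. Regression to the mean matters only conditionally on a chance baseline imbalance.
- **The size is not fixed by the document.** The 15–35% variance reductions for rho between 0.7 and 0.3 need equal standard deviations before and after surgery. If the spread widens after surgery, the gain may nearly vanish. To say that precision is thrown away would therefore claim too much.

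**Conclusion.** The point holds as a free improvement for secondary outcomes. Both stated rules for continuous data ignore the baseline value as a covariate, and asymptotically neither can beat a baseline-adjusted model. The direction is general. The size depends on rho, on the ratio of standard deviations and on an assumed 80% starting power, none of which the document gives. With equal standard deviations the variance reduction against the change score runs from 35% at rho 0.3 to 5% at rho 0.9. With other ratios it may be as little as 1–4%, or larger when follow-up is less variable than baseline. The loss is one of precision only. The primary outcomes, the sample size and the validity of the tests are untouched.

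**What to change.** Replace the sentence on changes from baseline with one to this effect: for each continuous or scored secondary outcome that has a baseline value, the post-treatment value will be compared between arms in a linear model with treatment and the baseline value of the same measure as terms. Skewed measures will be analysed on the log scale or by rank-based ANCOVA, and the adjusted difference (or ratio, on the log scale) will be reported with its 95% CI. Raw change from baseline stays as a descriptive summary.

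The cost is one sentence and one degree of freedom per outcome. No extra patients, visits or samples are needed if the baseline values are collected as the change rule implies, and the SPSS package already named fits the linear model. The article reports recruitment as ongoing, so at that stage the change could be made before the blind is broken.

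### A change-from-baseline analysis is set without limit although the primary times have no baseline, and the usable t/Mann-Whitney rule breaks down where an event is not observed

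*Protocol article*

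**What the plan says.** Under Outcome measures, the Protocol article lists as primary "time to first flatus, time to first defecation, time to first bowel sounds, time to consuming liquid/semi-liquid/general diet". All are times from surgery to a first event.

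Under Data collection and statistical analysis it gives several rules:

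- "Changes from baseline in outcome measurement among the two groups are analyzed using analysis of variance (ANOVA) or the Kruskal-Wallis test when appropriate". The sentence is not limited to any outcome.
- "All statistical tests are in a two-tailed t test at a 5% level of significance".
- Differences between groups are assessed with Student's "test for normally distributed continuous variables or the Mann-Whitney U test for skewed continuous variables".
- "Length of hospital stay is calculated using Kaplan-Meier analysis to compare differences between groups". This is the only time-to-event method named, and length of stay is not in the outcome list.
- "All missing data are analyzed using the last observation carried forward (LOCF) imputation method".
- "The ITT analysis will include all patients who were randomly recruited".

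Under Trial procedure, "Subjects will be evaluated at least three times per day", with results recorded until the patient leaves hospital. Table 1 allows elimination for, among other things, serious complications, infection, a second operation or refusal of further treatment.

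**The concern.** Two separate problems meet here.

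First, a time from surgery to first flatus has no value before surgery. A change from baseline cannot be formed for any primary outcome, yet the sentence that prescribes it excludes none of them.

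Second, the rules that can be applied to a time in hours (t test, Mann-Whitney) need a completed time for every patient. A patient who is discharged, or is no longer observed, before the event has only a lower bound. No stated rule handles that lower bound correctly. Carrying forward a last observation treats the moment observation ended as the moment of recovery, so the patient looks faster than he or she was. If the arms lose patients at different rates, the arm that loses more looks better.

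The primary comparison of a trial that calls itself pivotal is at stake.

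**Working it through.** **1. Can a change from baseline be formed?** Change = value after treatment minus value before. For a time to first event there is no value before. The only way to compute it is to set every baseline to 0, which makes the change equal to the time itself. With two groups, ANOVA on that time has F = t², the same p-value as the equal-variance t test. Kruskal-Wallis is Mann-Whitney apart from the continuity correction. So the sentence is either not computable for the primary outcomes or adds nothing to the t/Mann-Whitney rule.

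**2. The plan's own figures.** Inputs from Sample size estimation: mean time to first flatus 22.06 h and 26.78 h, difference 4.72 h, 89 per group, 15% dropout.

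- 89 / (1 − 0.15) = 104.7, rounded up to 105. This reproduces.
- The 89 cannot be reproduced, because the article states neither SD nor power. Solving back at two-sided 5%: SD = 4.72 × √(89/2) / (1.960 + z_power) = 31.49 / 2.802 = 11.24 h at 80% power, or 31.49 / 3.242 = 9.71 h at 90%.

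**3. What happens when events are unobserved.** Simulation with 3000 runs, 105 per group and the stated means; in the no-effect rows both means are 26.78 h. Assumptions not in the documents: Weibull times with shape 2.7 (placebo SD about 10.7 h), the given share of patients withdrawing at a time spread evenly over 0–24 h and unrelated to recovery speed, and the last time seen scored as the event for the t and Mann-Whitney tests. Log-rank censors at that time.

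| True effect | Withdrawal XBP / placebo | t | Mann-Whitney | Log-rank | Mean difference, placebo − XBP |
|---|---|---|---|---|---|
| 4.72 h | 0 / 0 | 93.6% | 89.8% | 96.2% | 4.7 h |
| 4.72 h | 15% / 15% | 80.3% | 72.5% | 93.8% | 4.1 h |
| 4.72 h | 10% / 20% | 48.3% | 39.1% | 93.9% | 2.8 h |
| none | 0 / 0 | 5.3% | 5.3% | 5.6% | 0.0 h |
| none | 15% / 15% | 5.2% | 4.8% | 5.4% | 0.0 h |
| none | 20% / 10% | 15.3% | 15.4% | 5.5% | 1.5 h |

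Entries are the share of runs with p < 0.05. Monte Carlo standard error is about √(0.05 × 0.95 / 3000) = 0.4 percentage points near 5%. With complete follow-up all three tests behave. Equal loss costs power and shrinks the difference. Unequal loss creates a false difference in favour of the arm that loses more.

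**4. Does the log-rank test cost power?** Under a Weibull model HR = (26.78 / 22.06)^shape, and events = 4 × (1.960 + 0.842)² / (ln HR)² for 80% power.

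- Shape 2.5: HR 1.62, 134 events; power at 210 events (2 × 105) 94%.
- Shape 2: HR 1.47, 209 events; power 80%.
- Shape 1: HR 1.21, 836 events. An exponential time has SD equal to its mean, 22.06 to 26.78 h, far above the 9.71 to 11.24 h implied by the plan's own 89.

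**5. Outcomes that do have a baseline.** Relative to a change score, ANCOVA has variance (1 − ρ²) / [2(1 − ρ)] = (1 + ρ)/2. At assumed baseline correlations of 0.3, 0.5 and 0.7 this is 0.65, 0.75 and 0.85, a reduction of 35%, 25% and 15%.

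**The case against.** The strongest reply is that the article does contain a workable test. The t/Mann-Whitney rule covers times in hours and matches a sample size built on a mean difference. The change-from-baseline sentence was probably meant for hormones and the electrogastrogram, and the t-test sentence is probably a slip for two-tailed, since chi-square, Fisher and Mann-Whitney tests stand beside it. This largely stands. A reader might infer that the primary outcomes have no valid test, or that three rival tests are open to choice. The documents do not support either: with two groups the named tests reduce to one parametric and one rank test, and both are sound when every event is observed.

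A reader might also infer that 15% of patients will lack an event time. That figure is a general dropout allowance in a trial with a 2-month follow-up, and many dropouts would come after the event. With assumed flatus times of 22 to 27 h and recording until discharge, unobserved flatus may be uncommon. Defecation and general diet are more exposed, but no rate is given.

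Nor does plain censoring remove bias if slow patients are the ones lost. Elimination for complications, infection or reoperation is plausibly related to bowel recovery, while log-rank and Cox assume that censoring is uninformative. The simulation makes withdrawal unrelated to recovery speed, which suits log-rank. This objection stands and shapes the fix.

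Finally, an additional file that is not shown may give more detail, and an article may leave a full censoring rule to it. That does not rescue the stated rules: LOCF for all missing data and an unlimited change-from-baseline sentence are in the text.

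**Conclusion.** The point holds in a limited form. The change-from-baseline analysis cannot be formed for any primary outcome, whatever the amount of censoring. The t/Mann-Whitney rule is usable only with complete event times, and the stated remedy for incomplete ones, LOCF, cannot supply a time for an event that was not seen. The only time-to-event method is attached to length of stay, which is not a listed outcome.

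The size of the harm is unknown, because the documents give no censoring rate. It is nil if every patient is followed to the event. Under the assumptions above, 15% early withdrawal in both arms lowers t-test power from 94% to 80%, and an imbalance of 20% versus 10% roughly triples the type I error. These are illustrations, not forecasts. The precision gain from ANCOVA is a secondary improvement that depends on an assumed correlation; a change score is not an error there.

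**What to change.** Before unblinding, reword the analysis section as follows:

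- **Primary times:** Kaplan-Meier curves and medians, with a log-rank test or Cox model stratified by surgery type and a stated time origin. The article says randomisation is stratified but does not name the factor; surgery type is assumed here because two operations are recruited.
- **Unobserved events:** use any event time recorded after elimination; otherwise censor at the last assessment. Remove LOCF for event times.
- **Sensitivity analysis for informative censoring:** for example, keep patients eliminated for complications or reoperation as event-free to a late time, such as the longest time observed in the trial, and report whether the conclusion changes.
- **Outcomes with a recorded baseline** (hormones, electrogastrogram and symptom scores where measured before treatment): limit baseline-based analyses to these and use ANCOVA with the baseline value.
- **The t-test sentence:** say only that all tests are two-tailed at 5%.
- **Length of stay:** list it as a secondary outcome or drop it.

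The cost is wording. Assessments at least three times a day already supply the censoring times, and no extra patients or data are needed. The small downside is that the effect appears as a hazard ratio and medians, to be reported beside the 4.72 h mean difference used for sizing.

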XBP is prescribed as standard in our hospital to promote recovery of gastrointestinal function after abdominal surgery. The function of XBP has been determined based on previous clinical practice, which has demonstrated that the prescription can safely and effectively restore gastrointestinal motility after abdominal surgery. We have conducted numerous research studies into gastrointestinal motility in recent years, and we consider that anesthesia and surgery lead to the POI, referred to as the syndromes, *Qi* deficiency and *Qi* stagnation, in Chinese medicine. XBP is a compound of *Panax ginseng* (*Renshen*), *Areca catechu* L. (*Binlang*), *Prunus persica* Batsch (*Taoren*), *Lindera aggregata* Kosterm (*Wuyao*), and *Fructus amomi* (*Sharen*). *P. ginseng* (*Renshen*) is an edible Chinese herb that promotes the production of body fluids and has a tranquilizing effect, and ginseng oligopeptides (GOP), small-molecular oligopeptides isolated from ginseng, have been proven to have anti-fatigue effects [7]. *A. catechu* L. (*Binlang*) has the function in Chinese medicine of promoting the circulation of *Qi*, and there is evidence that, one of its components, arecoline, affects gastrointestinal motility by direct binding to M receptors [8]. *P. persica* Batsch (*Taoren*) has the function in Chinese medicine of improving blood circulation and relaxing the bowels and there is evidence that its extract can lower blood viscosity [9]. *L. aggregata* Kosterm (*Wuyao*) has the function in Chinese medicine of promoting *Qi* circulation to relieve pain and one of its components. Total alkaloids have anti-inflammatory and analgesic effects [10]. *F. amomi* (*Sharen*) has the functions in Chinese medicine of removing dampness to restore the normal function of the stomach, while its water extract has a role in promoting gastrointestinal peristalsis [11].

Here, we describe a protocol for a double-blind, randomized controlled, clinical trial to evaluate the safety and efficacy of the use of XBP to promote gastrointestinal function recovery after abdominal surgery.

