### Participants

Participants who have undergone laparoscopic radical resection of rectal carcinoma in the Gastrointestinal Surgery Department or laparoscopic panhysterectomy of benign lesions in the Gynecology Department of Guangdong Provincial Hospital of Traditional Chinese Medicine will been recruitment. The inclusion, exclusion, and elimination criteria are listed in Table 1.

**Table 1 Tab1:** Inclusion, exclusion, and elimination criteria

Category	Criteria
Inclusion criteria	Patients who have undergone surgery for gastric or colorectal cancer, or hysterectomy for hysteromyoma Age 40–75 years old Duration of surgery, 1–4 h Time under anesthesia, 1.5–4.5 h TCM syndrome, Qi deficiency and Qi stagnation Provision of signed, informed consent
Exclusion criteria	Advanced malignant tumor cachexia, extreme weakness Malignant tumors requiring extended radical surgery Cardiovascular, liver, kidney, brain, or lung co-morbidity, or other serious diseases Poorly controlled hypertension or diabetes Mental disability Allergy to the intervention Pregnant or breast-feeding women Severe malnutrition (serum albumin < 21 g/L, pre-albumin < 0.1 g/L) Repeated abdominal surgery and severe intestinal adhesions Blood loss > 400 mL during surgery Serious complications occurring within 6 h after surgery (e.g., multiple organ dysfunction) Postoperative intraperitoneal hyperthermic perfusion Emergency surgery Prokinetic drugs prescribed after surgery Patient participating in another clinical study, or having participated in another clinical study in the previous month Patient considered inappropriate to participate the study by clinical investigators
Elimination criteria	Do not meet the inclusion criteria, but mistakenly included Worsening condition that cannot be controlled in 3 days Other complications because of interventions, including severe allergy or serious adverse events Serious complications, infection, or requiring a second operation during treatment Refusal to continue the treatment, regardless of the reason

*TCM* traditional Chinese medicine

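### The primary recovery times are compared by valid but unadjusted two-group tests that leave out the randomization stratum and operative variables already needed for eligibility, which gives up some precision of unknown size

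*Protocol article*

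**What the plan says.** All references are to the protocol article.

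- **Outcomes.** Outcome measures lists "Primary outcome measures: time to first flatus, time to first defecation, time to first bowel sounds", followed by the times to the diet stages.
- **Tests.** Data collection and statistical analysis sends between-group differences to Student's t test for "normally distributed continuous variables or the Mann-Whitney U test for skewed continuous variables". Changes from baseline "are analyzed using analysis of variance (ANOVA) or the Kruskal-Wallis test when appropriate". No covariate or stratum is named for any efficacy comparison. The only time-to-event method serves another outcome: "Length of hospital stay is calculated using Kaplan-Meier analysis to compare differences between groups".
- **Randomization.** The Randomization section states a stratified design but does not name the factor.
- **Eligibility.** Table 1 (Participants) sets "Duration of surgery, 1–4 h Time under anesthesia, 1.5–4.5 h" as inclusion criteria and "Blood loss > 400 mL during surgery" as an exclusion criterion.
- **Timing.** Under Trial procedure, participants are to "take the medicine twice every day after surgery (excluding the surgery day" itself, so the operative values exist before any dose.
- **Prognosis.** The Background says "we consider that anesthesia and surgery lead to the POI". The Discussion also lists surgical trauma and the effects of anesthesia among the causes of postoperative gastrointestinal dysfunction.

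**The concern.** The article holds that the operation and the anesthetic slow the gut, and it limits both by eligibility. Within those limits, operating time may still differ fourfold between patients (1 to 4 h), and the two operations are quite different. Any variation in recovery that comes from these sources goes into the error term of an unadjusted test. The randomization stratum is used for allocation and then dropped from the comparison.

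At stake is efficiency: wider intervals and less power than the available data might allow. The operative variables are fixed before dosing, so treatment cannot influence them and adjusting for them is legitimate. Since the article fixes the unadjusted tests in so many words, this is a comment on a stated method and not on an omitted detail.

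**Working it through.** **Inputs from Sample size estimation.** Mean time to first flatus is 22.06 h against 26.78 h, so δ = 26.78 − 22.06 = 4.72 h. The article gives 89 per group, 15% dropout, 105 per group and 420 in total. The test level is two-sided 5% (Data collection and statistical analysis).

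**Inputs that are assumed.** The article states neither SD nor power, so I take power as 80% or 90% and back-solve the SD. It gives no R² either; I use 5% to 20%.

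**The plan's own figures.** 89/(1 − 0.15) = 104.7, rounded up to 105, which agrees. 4 × 105 = 420, which fits 105 per arm within each of two operation types, although the article does not say that the operations are analyzed separately. The 89 itself cannot be reproduced without an SD and power.

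**Back-solved SD** (normal approximation): SD = δ × √(n/2) / (z₀.₉₇₅ + z_power), with √(89/2) = 6.671.
- 80% power: 4.72 × 6.671 / (1.960 + 0.842) = 11.24 h.
- 90% power: 4.72 × 6.671 / (1.960 + 1.282) = 9.71 h.

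The noncentral t gives nearly the same values, 11.18 h and 9.66 h.

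**Gain from a linear model in hours.** Residual SD = SD × √(1 − R²). Power at 89 per arm = Φ[(z₀.₉₇₅ + z_power)/√(1 − R²) − 1.960]. Equivalent unadjusted n = 89/(1 − R²).

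| Assumed R² | √(1 − R²) | Interval narrower by | Power from 80% | Power from 90% | Equivalent n per arm |
|---|---|---|---|---|---|
| 5% | 0.975 | 2.5% | 82.0% | 91.4% | 94 |
| 10% | 0.949 | 5.1% | 84.0% | 92.7% | 99 |
| 20% | 0.894 | 10.6% | 88.0% | 95.2% | 111 |

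**If both operations are pooled with the same SD.** There would be 2 × 89 = 178 evaluable patients per arm. With SD 11.24 h, unadjusted power for flatus is 97.7%, rising to 98.7% at R² = 10% and 99.3% at 20%. With SD 9.71 h it starts at 99.6%.

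**If pooling widens the SD.** Suppose the stratum is operation type (not stated), with equal numbers and a mean gap g between types. Then pooled SD = √(SD² + g²/4). With SD 11.24 h and 178 per arm:
- g = 6 h: pooled SD 11.63 h, unadjusted power 96.9%.
- g = 12 h: pooled SD 12.74 h, unadjusted power 93.8%.
- g = 24 h: pooled SD 16.44 h, unadjusted power 77.3%.

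Adjusting for the stratum brings each back to 97.7%. The gaps are illustrations; the article gives none.

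**Cost if three covariates explain nothing.** Variance factor = (2n − 3)/(2n − 3 − 3 − 1). At 89 per arm this is 175/171 = 1.023, about 2%. At 178 per arm it is 353/349 = 1.011, about 1%.

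**The case against.** The strongest reply is that nothing here is an error. Randomization makes an unadjusted t test or Mann-Whitney test valid, and chance imbalance in operating time is already covered by the test's error rate. That stands. A reader might infer that the planned tests are biased or inflate the type I error; the article gives no ground for that.

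Second, the size is assumed throughout. A reader might take the 82% to 88% as a demonstrated loss, but SD, power and R² are all missing from the article. The eligibility limits on operating time, anesthesia time and blood loss may keep R² modest, and at 5% the gain is about 2 power points. For flatus in a pooled analysis there is little left to gain. This stands too, with two limits: only flatus was sized among several primary times, and the planning figures come from gynecologic transabdominal surgery, so the SD for rectal resection has no support in the article.

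Third, the prognostic evidence is indirect. The article says that surgery and anesthesia cause the dysfunction. It does not say that longer surgery within 1 to 4 h, or more blood loss below 400 mL, predicts slower recovery, and it offers nothing of this kind for age. The operative covariates are therefore plausible on the article's own reasoning but unproven, and age is optional.

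Fourth, a reader might apply the power figures to a Cox or log-time model. They do not carry over: √(1 − R²) scaling belongs to a linear model in hours, adjustment changes what a hazard ratio estimates, and log time replaces the 4.72 h difference with a ratio.

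Finally, covariates are often left to an analysis plan. But this article does name the tests, and none of them uses the stratum.

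**Conclusion.** The point holds as a modest efficiency improvement to a stated method. The article fixes valid but unadjusted tests for its primary recovery times. It thereby ignores its own randomization stratum and pre-treatment operative values that must be known for every eligible patient.

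The direction of the loss follows if these variables predict recovery, as the article's account of causes suggests. Its size cannot be taken from the article. The range of about 2 to 8 power points from an 80% base rests on three assumptions: the back-solved SD, R² of 5% to 20%, and analysis at 89 per arm. For flatus with all 420 pooled and the same SD, the gain is about 1 to 2 points. The stratum matters most where the two operations are pooled and differ clearly in recovery time.

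**What to change.** In Data collection and statistical analysis, and before unblinding, pre-specify one adjusted model for each recovery time, with treatment, the randomization stratum, duration of surgery (continuous) and intraoperative blood loss. Where every time is observed, ANCOVA on hours is a suitable example and keeps the scale on which the trial was sized. Use one of surgery or anesthesia duration, since the two are likely to overlap. Age may be added but is not needed. Keep the unadjusted test as a sensitivity analysis. Whether to move to a survival model is a separate decision.

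The cost is small. Duration and blood loss must be entered as continuous values and not only as a passed eligibility check, which the article does not confirm. One model must be fixed in advance, and the estimate becomes conditional on its covariates. Three uninformative covariates would cost about 2% in variance at 89 per arm. The article reports recruitment as ongoing, so at that point the change could still precede unblinding.
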